## Abstract

**Background:**

Cervical cancer (CC) is nearly always caused by persistent human papillomavirus (HPV) infection. It is the most common cancer among women living with HIV (WLWH) and is the leading cause of cancer-related death in women in East Africa, with 10,241 new cases reported in Tanzania in 2020. In 2019, the World Health Organization (WHO) presented a global strategy for the elimination of CC as a public health problem, proposing targets to meet by 2030 for HPV vaccine coverage (90% of all 15-year-old girls), CC screening (70% of all women once at 35 and again at 45 years of age) and treatment delivery, to be scaled at national and subnational levels with a context-sensitive approach. This study aims to evaluate the upscaling of screening and treatment services at a rural referral hospital in Tanzania in order to address the second and third WHO targets.

**Methods:**

This is an implementation study with a before-and-after design performed at St. Francis Referral Hospital (SFRH) in Ifakara (south-central Tanzania). CC screening and treatment services are integrated within the local HIV Care and Treatment Center (CTC). The standard of care, consisting of visualization of the cervix with acetic acid (VIA) and cryotherapy has been up-scaled with self-sampled HPV testing and also involved the introduction of mobile colposcopy, thermal ablation and loop electrosurgical excision procedure (LEEP). Participants are WLWH aged 18 to 65 years. Outcome measures included the percentage of women screened, HPV prevalence and genotype, and adherence to screening, treatment and follow-up plan. Additionally, we will explore the performance of novel diagnostic tests (QG-MPH®, Prevo-Check® and PT Monitor®), which share the features of being manageable and inexpensive, and thus a potential tool for effective triage in HPV high-prevalence cohorts.

**Discussion:**

The study will provide relevant information about HPV prevalence and persistence, as well as reproductive and lifestyle indicators in a CC high-risk cohort of WLWH and about upscaling screening and treatment services at the level of a rural referral hospital in Tanzania. Furthermore, it will provide exploratory data on novel assays.

**Trial registration:**

ClinicalTrials.gov Identifier: NCT05256862, date of registration 25/02/2022. Retrospectively registered.

**Supplementary Information:**

The online version contains supplementary material available at 10.1186/s12913-023-09113-3.

## Background

Cervical cancer (CC) most frequently arises from persistent infection with oncogenic high risk (HR-) human papillomavirus (HPV) types [1]. Due to global disparities in access to health care services and concurrent epidemiological risk factors (e.g., HIV infection), CC remains a major cause of morbidity and premature mortality in many low- and middle-income countries (LMICs). Despite availability of effective methods for prevention, early diagnosis and treatment [2–7], women living with HIV (WLWH) have a sixfold higher risk of acquiring HPV infection and developing cancerous lesions [8], even at younger ages [9, 10].

The World Health Organization (WHO) is leading a global effort to eliminate CC as a public health problem, proposing the “90–70-90” targets to meet by 2030: 90% of girls fully vaccinated against HPV by 15 years of age; 70% of women screened using a high-performance test by 35 years of age and again by 45 years of age; 90% of women identified with CC treated and given care [11].

The United Republic of Tanzania, where this study is planned, has the highest incidence of CC in East Africa, with 10,241 new cases diagnosed in 2020, a cumulative risk of 25.3% of new cases and 24.2% of cancer-related deaths per year according to the IARC/WHO Report [12]. Among WLWH, high-risk HPV (HR-HPV) positivity rates have been reported to be as high as 46.7% [13]. Cohorts based in Dar es Salaam, Moshi and Mwanza are currently also being investigated with regard to the distribution of different HPV genotypes [14].

CC is preventable with HPV vaccination. Following a successful pilot project in 2014 in the Kilimanjaro region among girls aged 9 – 14 years, in 2018 the Ministry of Health (MoH) of Tanzania introduced nationwide vaccination as a school-based program for 14-year-old girls [15], reaching an estimated coverage of 78% for the first dose and 49% for the second dose by the end of 2019 [16]. Nevertheless, the limitation of vaccination is the insufficient coverage of all HR-HPV types and a large and older non-vaccinated population, necessitating ongoing secondary prevention. In 2011, the MoH of Tanzania had successfully established a nationwide screen-and-treat program using speculum-aided visual inspection with acetic acid (VIA) and cryotherapy for precancerous lesions [15]. Given the higher risk for WLWH, screening is recommended at the time of HIV diagnosis and then annually [17], optimally integrated into routine HIV care, together with screening and treatment of sexually transmitted infections (STI) and female genital schistosomiasis (GS) [18].

VIA is used to identify acetowhite lesions, which if eligible according to the WHO guidelines, are treated with cryotherapy or thermal ablation.

While VIA, as well as cryotherapy for VIA positive (VIA +) minor changes can be provided effectively at a district level, many factors, including disease perception, stigma, equipment, and personnel availability can affect the uptake [15, 17]. Moreover, previous studies in Tanzania reported up to 30% of women with documented precancerous lesions not receiving cryotherapy immediately after diagnosis, and around 80% of them subsequently being lost to follow-up [15]. Further steps in the cascade of care, in the case of larger lesions or invasive cervical cancer (ICC), are hampered by additional factors including geographic confinement of cancer clinics as well as cost of service [15, 17]. Data on the number of women not receiving loop electrical excision procedure (LEEP) although indicated and/or not referred to cancer facilities once a diagnosis has been confirmed are unavailable.

In order to meet the WHO targets, higher coverage of screening services and scaling-up of existing screening points with more sensitive and specific methods such as HPV-testing, and therapeutic options for severe dysplasia/ICC such as LEEP within a same-day-screen & treat approach, is urgently needed [18–20]. As of 2021, HPV testing is already part of routine screening programs in 48 countries, mainly, but not exclusively, in Europe and America, thanks to the roll-out of molecular diagnostic platforms [21]. If performed on self-collected samples, it is a cost-effective and time saving approach which improves screening uptake due to better acceptance compared to physician collected samples [22–26]. Self-sampling has been proven effective in sub-Saharan African countries, with a reported sensitivity of 88–96.7% and specificity of 32.1–82.8% [27]. Moving to an HPV-based strategy has two major limitations: the same-day screen & treat approach depends on the analysis turnaround time of HPV tests, and secondly it has low specificity for severe dysplasia / ICC [28] in populations with high HPV prevalence. Based on this rationale, novel serological tests that target antibodies against HPV-oncogenic protein complexes and mRNA-based technologies targeting dysplasia-specific biomarkers are being explored in this study as well. These tests could allow direct identification of patients requiring treatment and spare the need for conventional pathological examinations, for which equipment and expertise is lacking in the country (Supplementary material: Annex A1 und A2).

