## Methods/design

### Study design

This is a before-and after study to evaluate the impact and feasibility of upscaling CC screening and treatment services for WLWH attending a rural referral CTC in Tanzania. The main objective is to evaluate the uptake by WLWH attending screening after implementation of HPV testing on a self-sampled cervico-vaginal smear, compared to a retrospective cohort screened by VIA. HPV testing has been implemented in a bundle with: a) a smartphone integrating a mobile colposcope (EVA system, Mobile ODT, Israel) for digital enhancement of VIA examination with cervix magnification and second look/quality control; b) thermal ablation in place of cryotherapy (thus avoiding the need for replenishing nitrogen gas cartridges); and c) LEEP.

We adopted an uncontrolled before-and-after design to compare proportion of WLWH attending screening before and after implementing mentioned interventions. A sub-study with cross-sectional design aims to explore diagnostic performance of two novel tests: the first, QuantiGene-Molecular-Profiling-Histology (QG-MPH), is based on transcriptomic biomarker analysis, while the second is a serological assay to detect antibodies against HPV16-L1 [29], either with a qualitative (Prevo-Check®) or quantitative (PT Monitor®) approach (Table 1. Supplementary material Annex A1 and A2). Further objectives are to determine the adherence to recommendations after screening, to assess the prevalence of HPV genotype-specific infection as well as other co-infections, and to assess feasibility, acceptability and costs of the new implemented screening and treatment plan.

**Table 1 Tab1:** Novel assays

Test	Name	Target	Description
Lateral Flow Assay (LFA)	PT Monitor® (Abviris GmbH, Germany)	HPV16-L1 Ab	Blood-based (serum) competitive immunoassay assessing the presence of epitope-specific antibodies against HPV16-L1. Elevated levels of these antibodies are associated with the presence of HPV16-induced cancer or pre-cancer. A quantitative readout is possible with an optical table-top reader (aLF reader by Qiagen, Germany). CE-marked IVD
Rapid Lateral Flow Assay (rLFA)	Prevo-Check® (Abviris GmbH, Germany)	HPV16-L1 Ab	Qualitative (yes/no) output of LFA (PT Monitor®) in form of rapid capillary point-of-care test with a cut-off of HPV16-L1 Ab > 1000 ng/ml. CE-IVD-marked for the detection of HPV16-induced anal and oropharyngeal cancers

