#### Laboratory analysis

The samples will be stored at room temperature and brought to the IHI laboratory, located next to the SFRH, at the end of the day. Serum will be obtained from the whole blood sample for quantification of antibodies to the HPV16-L1 DRH1 epitope (PT Monitor®, Abviris, Germany). After pre-incubation of 25 µL serum with an HPV16-L1-specific reagent for 5 min, the mixture is transferred onto a lateral flow test cassette. The test result is measured 15 min later with a table-top reader (Qiagen, Germany).

Self-collected cervico-vaginal smear samples are used for HPV testing and QG-MPH, an innovative patented assay by Charité-Universitätsmedizin Berlin (Charité), Berlin, Germany (Charité Technology Transfer, patent WO2020/161285 A1) based on QuantiGene 2.0 (ThermoFisher Inc., Waltham, MA, USA) platform technology. QG-MPH has promising results for detecting CIN3 + with 90% accuracy (i.e., high sensitivity and specificity), and could become a quick onsite-triage method and a pathology-replacing, molecular diagnostic assay [34]. Further details are provided in Annex A2.

The cervico-vaginal swab is fixed in a methanol-based transport medium (ThinPrep® PreservCyt® solution, Hologic N.V., Belgium). HPV testing takes place in two steps: DNA extraction will be performed at IHI Laboratory in Ifakara, where samples undergo temporary storage at -20 °C. Every 1–2 weeks, a batch of 200–400 samples will be transported to the IHI Laboratory in Bagamoyo for PCR-based DNA amplification with the Seegene Anyplex™ II 28 HPV Detection Test (Seegene Inc., Korea), an RT-qPCR assay designed to detect and individually genotype 19 different HR-HPV types (HPV 16, 18, 26, 31, 33, 35, 39, 45, 51, 52, 53, 56, 58, 59, 66, 68, 69, 73 and 82) and 9 low risk (LR)-HPV genotypes (i.e. HPV 6, 11, 40, 42, 43, 44, 54, 61 and 70) in 2 parallel wells. Staff training and laboratory setup for transcriptome analysis in Tanzania was recently hindered by the SARS-CoV-2 pandemic. CFX96™ Dx Real-time PCR System was not lent to the IHI branch of Ifakara because of shortages of the instrument in East Africa. A cervico-vaginal smear sample aliquot will also be shipped for further transcriptome analysis at the HPV laboratory of Charité according to the MTA (Material Transfer Agreement).

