### Endpoints

The primary endpoint is screening coverage, defined as the proportion of WLWH enrolled in KIULARCO screened for CC in the 12 months period after implementation of HPV testing. Participants that undergo screening and transfer out to other CTC within the study period are also included. Secondary endpoints are listed in Table 3.

**Table 3 Tab3:** Endpoints

	Endpoint
**HPV prevalence & persistence**	Proportion of participants with documented HR-HPV, LR-HPV and HPV negative at baseline
	HPV genotypes at baseline
	Proportion of participants with documented HR-HPV, LR-HPV and HPV negative at follow up (6 months after the first sample)
	HPV genotypes at follow up (6 months after the first sample)
	Rate of clearance and persistence of HPV at 6 months follow-up and factors associated with viral persistence
**Cervical lesions**	Prevalence of cervical dysplasia among the patients with HR-HPV
	Prevalence of co-infection (STI and GS)
**QG-MPH® performance**	Prevalence of HSIL/CC detected by QG-MPH® in cervical smear samples
	Diagnostic test accuracy (sensitivity, specificity, PPV, NPV) in detecting patients with CIN3 + compared to colposcopy images, HPV infection detected by Seegene Anyplex ™ II 28 and histology
**Prevo-check® performance**	Prevalence of HPV16 positive CIN2 + detected by Prevo-check®
	Diagnostic test accuracy (sensitivity, specificity, PPV, NPV) in detecting patients with HPV 16 compared to Seegene Anyplex ™ II 28
**PT Monitor® performance**	Comparison of HPV16-antibody levels in women with and without HPV16-positive CIN2 + . Calculation of test performance parameters (sensitivity, specificity, PPV, NPV) at different antibody thresholds and calculation of optimum cut-off for CIN2 + detection by ROC analysis and Youden index
	Diagnostic test accuracies (sensitivity, specificity, PPV, NPV) in detecting patients with HPV16-induced CIN2 + by PT Monitor® compared to colposcopy images, HPV infection detected by Seegene Anyplex ™ II HPV 28 Detection and histology
**Screening strategy implementation**	Acceptability of cervical self-sampling
	Acceptability of proposed implemented pathway
	Adherence to follow-up
	Rate of WLWH completing the CC screening and treatment care plan
	Prevalence of cryo/thermoablation-non-eligible lesions treated with LEEP

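### The serological tests are put forward for triage of any lesion needing treatment, but no accuracy row in Table 3 clearly measures them against CIN2+ of any HPV type

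*Protocol article*

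**What the plan says.** **Intended use.** The Background describes the problem of low HPV-test specificity for severe disease where HPV is common, and then says that "novel serological tests that target antibodies against HPV-oncogenic protein complexes and mRNA-based technologies targeting dysplasia-specific biomarkers are being explored". Of the two kinds of test together it says: "These tests could allow direct identification of patients requiring treatment and spare the need for conventional pathological examinations". The Methods part of the Abstract names QG-MPH, Prevo-Check and PT Monitor and describes them as manageable and inexpensive, "thus a potential tool for effective triage in HPV high-prevalence cohorts". Neither place restricts the use to HPV16 disease.

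**Who is treated.** Under Physical examination / mobile colposcopy and under Therapy, treatment depends on VIA findings and lesion severity. Genotype plays no part. Under Laboratory analysis, the HPV assay can "individually genotype 19 different HR-HPV types"; HPV16 is one of them.

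**What the assay measures.** Table 1 gives the serological target as HPV16-L1 antibody and says of PT Monitor: "Elevated levels of these antibodies are associated with the presence of HPV16-induced cancer or pre-cancer".

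**What Table 3 will estimate.**
- PT Monitor, first row: "Comparison of HPV16-antibody levels in women with and without HPV16-positive CIN2"+, then sensitivity, specificity, PPV and NPV at several thresholds, then a ROC/Youden cut-off for CIN2+ with no type stated.
- PT Monitor, second row: accuracy "in detecting patients with HPV16-induced CIN2 + by PT Monitor® compared to colposcopy images", HPV infection by the genotyping assay, and histology.
- Prevo-Check: the prevalence of HPV16-positive CIN2+ that it detects, and accuracy for HPV16 infection against the genotyping assay.
- QG-MPH: accuracy for CIN3+, with no type restriction.

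**The concern.** A triage test is judged by how well it separates women who have a lesion needing treatment from those who do not. If only HPV16-induced CIN2+ counts as disease, CIN2+ caused by any of the other 18 high-risk types falls in the non-diseased group. A woman with such a lesion and a negative antibody test is then scored as a correct negative, although the stated use would require the test to find her.

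The HPV16-limited target is a fair question about what the assay detects, but it does not answer the triage question. The sub-study could report a reassuring sensitivity and NPV that readers carry over to the use described in the Abstract and Background, where the figures may be much lower. Prevo-Check has the same gap in another form: its accuracy row contains no lesion.

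**Working it through.** The protocol gives no sample size, prevalence or expected accuracy for the serological tests, so there is no planned figure to reproduce. The check has two steps: what follows from the definitions alone, and an illustration of size.

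**1. From the definitions.** Split the women into three groups: HPV16 CIN2+, other-type CIN2+, and no CIN2+. Call the antibody-negative counts a, b and c.
- NPV, HPV16-only target = (b + c)/(a + b + c).
- NPV, any-type target = c/(a + b + c).

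The denominator is the same, so the HPV16-only NPV is never lower, and it is higher whenever b > 0. By the same argument the HPV16-only PPV is never higher than the any-type PPV.

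For sensitivity, let s be the HPV16 share of CIN2+, Se the positivity in HPV16 CIN2+, and f the positivity in other-type CIN2+. Any-type sensitivity = s·Se + (1 − s)·f. This is below Se whenever f < Se, which is what one expects of an HPV16-L1 assay.

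Specificity moves only if positivity in other-type CIN2+ differs from that in women without CIN2+. Antibody-positive women with other-type CIN2+ count as false positives under the HPV16-only target, so the change can go either way.

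**2. Illustration.** From the documents: 1200 women (Sample size) and HR-HPV positivity of 46.7% in women living with HIV (Background), so 0.467 × 1200 ≈ 560 HR-HPV-positive women. Assumed, because the documents give nothing: CIN2+ in 15%, HPV16 share 30%, positivity 80% in HPV16 CIN2+ and 10% in all other women, and every woman's lesion status known.

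| Group | N | Antibody + | Antibody − |
|---|---|---|---|
| HPV16 CIN2+ | 25.2 | 20.16 | 5.04 |
| Other-type CIN2+ | 58.8 | 5.88 | 52.92 |
| No CIN2+ | 476 | 47.6 | 428.4 |
| Total | 560 | 73.64 | 486.36 |

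| Measure | HPV16-only target | Any-type CIN2+ |
|---|---|---|
| Sensitivity | 20.16/25.2 = 80% | 26.04/84 = 31% |
| Specificity | 481.32/534.8 = 90% | 428.4/476 = 90% |
| NPV | 481.32/486.36 = 99.0% | 428.4/486.36 = 88.1% |
| PPV | 20.16/73.64 = 27.4% | 26.04/73.64 = 35.4% |

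Of the 84 women with CIN2+, 5.04 + 52.92 ≈ 58 are antibody-negative.

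**Range**, with positivity still 80% and 10%:

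| CIN2+ | HPV16 share | Any-type sensitivity | NPV, HPV16-only | NPV, any-type |
|---|---|---|---|---|
| 10% | 20% | 24% | 99.5% | 91.4% |
| 10% | 50% | 45% | 98.8% | 93.6% |
| 20% | 20% | 24% | 99.1% | 82.6% |
| 20% | 50% | 45% | 97.6% | 86.7% |

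A different set of assumptions (1200 women, CIN2+ in 10%, 5% positivity in other women, HPV16 share 20%, 40%, 60%) gives any-type sensitivity of 20%, 35%, 50% against 80%, and NPV of 91.4%, 92.9%, 94.5% against 99.6%, 99.1%, 98.7%.

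**The case against.** **The first PT Monitor row may already cover this.** It lists all four accuracy measures and a cut-off for CIN2+ with no type stated. This stands in part. Read alone, the clause could mean any type. But the row opens by grouping women by HPV16-positive CIN2+, so its target is ambiguous, and the second row is explicit: "in detecting patients with HPV16-induced CIN2 + by PT Monitor". It offers nothing for Prevo-Check.

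**The pathology-replacing claim belongs to QG-MPH.** Laboratory analysis does spell out that role for QG-MPH, whose accuracy row has no type restriction. But the Background sentence covers the serological tests too, and the Abstract names both of them as potential triage tools.

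**The HPV16 limit is disclosed, the wording is tentative, and the sub-study is exploratory.** All true: Table 1 states the target, the rationale is cautious, and Statistical analysis sets no hypothesis for secondary endpoints. This limits the weight of the point. It does not remove it, because an exploratory estimate must still address the use for which it is offered.

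**A reader might infer that women with CIN2+ would go untreated.** The documents do not support that. HR-HPV-positive women are called for examination whatever their serology, and a positive rapid test only adds women to same-visit examination (Physical examination / mobile colposcopy; Follow-up). No passage says that a negative antibody result would spare an HR-HPV-positive woman examination. Where the tests might later sit in the pathway is marked in Fig. 1, with assay details in Annexes A1 and A2; none of these is available here.

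**A reader might also infer that specificity is inflated.** The illustration shows none: it is 90% under both targets.

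**Prevo-Check has a lesion-based row.** It does, for the prevalence of HPV16-positive CIN2+ detected. That row is still limited to HPV16 and is not an accuracy measure.

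**Conclusion.** The concern holds as a mismatch between stated use and endpoint. Table 3 contains no serology accuracy row that clearly takes CIN2+ of any type as its target, while the Abstract and Background describe a use that needs one. That the HPV16-only NPV exceeds the any-type NPV follows from the definitions once any other-type CIN2+ is antibody-negative. That sensitivity also looks better rests on the assay reacting less often in other-type disease, as its design suggests. PPV moves the other way.

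The size is unknown. The 24% to 45% sensitivity and 83% to 94% NPV, against 80% and 97.6% to 99.5% as defined, rest wholly on the assumed CIN2+ prevalence, HPV16 share and positivity rates, and on complete verification. They show that the gap could be large, not what it will be.

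The consequence is confined to interpreting an exploratory sub-study. The HPV16-limited endpoint is valid for what it measures. The change is worth making because it decides whether the sub-study can speak to triage at all.

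**What to change.** 1. Keep the HPV16-limited results for PT Monitor and Prevo-Check, and label them type-specific.
2. In the PT Monitor row with thresholds and the ROC/Youden cut-off, state which CIN2+ is the target, and reconcile the two PT Monitor rows.
3. For both serological tests, also report sensitivity, specificity, PPV and NPV with 95% confidence intervals against CIN2+ of any HPV type among HR-HPV-positive women, with Prevo-Check at its fixed cut-off. Use the reference information already planned, and state its limits.
4. State that any conclusion on triage, or on identifying women who need treatment, rests on the any-type result.

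The cost is one further set of two-by-two tables from data already planned for collection. No endpoint is lost and no procedure changes. The downside is that the triage sensitivity and NPV will probably be less favourable.
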